## Abstract

Children with speech sound disorders benefit from feedback about the accuracy of sounds they make. Home practice can reinforce feedback received from speech pathologists. Games in mobile device applications could encourage home practice, but those currently available are of limited value because they are unlikely to elaborate “Correct”/”Incorrect” feedback with information that can assist in improving the accuracy of the sound. This protocol proposes a “Wizard of Oz” experiment that aims to provide evidence for the provision of effective multimedia feedback for speech sound development. Children with two common speech sound disorders will play a game on a mobile device and make speech sounds when prompted by the game. A human “Wizard” will provide feedback on the accuracy of the sound but the children will perceive the feedback as coming from the game. Groups of 30 young children will be randomly allocated to one of five conditions: four types of feedback and a control which does not play the game. The results of this experiment will inform not only speech sound therapy, but also other types of language learning, both in general, and in multimedia applications. This experiment is a cost-effective precursor to the development of a mobile application that employs pedagogically and clinically sound processes for speech development in young children.

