### Aims and objectives

This study is the first step toward our long-term objective to create a Virtual Speech Therapist that employs pedagogically and clinically sound processes for speech development in young children to assist with home practice as part of therapy with a speech pathologist. Automatic speech recognition (ASR) systems are complex and time-consuming to develop. Sophisticated algorithms are required to cover all possible pronunciations, correct and incorrect, in different voices and background noise conditions (Renals and King, 2010). In speech and language learning, they may identify correct pronunciation as incorrect and vice-versa (Massaro and Light, 2004; van Doremalen et al., 2016). Our study will investigate the effectiveness of different types of feedback for speech sound substitutions occurring in phonological disorders, unhindered by confounding problems in automatic speech recognition (Massaro and Light, 2004) and before committing resources to the development of complicated software.

This study aims to employ a “Wizard of Oz” design to evaluate the efficacy within a multimedia platform of four types of feedback to assist speech development in young children. In particular, the study aims to compare predominant types of feedback given by speech pathologists during minimal pair therapy, and those recommended in learning literature, with those recommended for multimedia learning.

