**Figure 3 F3:**
[figure not shown]
Study design.

Children will be randomly allocated to one of four experimental groups or to a control group. For type of feedback, verification feedback types KR/MT/RUC are not highly recommended because they do not supply information to guide the learner. However, KR/MT will be included because it is prevalent in multimedia applications, mainly because it is easy to implement. RUC will be excluded because the number of attempts cannot be controlled and because it may inhibit the timely progress of some children. Intrinsic feedback is recommended for multimedia applications because it can assist learning by building upon, and relating to learners' real-world experience (Laurillard, 2002, pp. 58–69; Ke, 2014). We are interested in comparing these two types of feedback in an attempt to verify the value of the less easily implemented intrinsic feedback. KP will also be included because it is arguably the most effective type of formative feedback (Shute, 2008) and also because it is prevalent in speech pathology practice (e.g., Maas et al., 2008). Whereas, KR/MT and intrinsic feedback can be provided alone or in combination with other types of feedback, KP usually follows and elaborates another type of feedback. Consequently, two types of feedback (KR/MT and Intrinsic) will be provided in isolation to highlight their differences and a further two will combine them with KP. The combined KR and KP condition will allow us to more closely simulate speech pathology sessions whereas the combined intrinsic and KP condition is recommended as best practice for multimedia environments. A fifth condition will act as a control for changes in speech development which could occur over time, either naturally or because of other interventions. KCR will not be provided as feedback because it will appear as a prompt when the sound is presented to the child. Table 3 summarizes the rationale behind the choices of types of feedback to be compared in the study. Table 4 presents examples of feedback provided to each experimental group.

**Table 3 T3:** Rationale for feedback type in experimental conditions.

**Group**	**Rationale for use of type of feedback in treatment**	**Feedback type**
1	Prevalent in multimedia applications for speech production because it is easy to implement.	KR/MT

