### Session schedule

Dosage is a significant variable in intervention for speech sound disorders (Baker, 2012; Kaipa and Peterson, 2016) and relates to the number of treatment sessions, the frequency of treatment sessions, length of treatment sessions and number of trials per treatment session (Baker, 2012). A clear precedent has not been set in the literature as to the most effective or efficacious dosage for phonological therapy, let alone home practice (which the study is aiming to investigate). There is evidence to suggest that treatment should occur three times per week (Allen, 2013) but daily home practice is also used (Crosbie et al., 2005). The number of sessions rarely exceeds 16–21 sessions in total in studies of phonological therapy (Crosbie et al., 2005; Williams, 2012). Despite the novelty of the study in exploring practice with an app the above literature will be used as a guide such that each participant will attend the Swinburne Babylab facility for individual sessions 3–4 days per week over a 2–4 week period for a total of 12 sessions (in addition to testing sessions). As the study seeks to investigate the number of trials (from data on percentage accuracy per trial) and length of session as measures of effectiveness of feedback and motivation, respectively, these parameters of dosage will not be set but we expect that children will engage for up to 20 min completing 80–100 trials.

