At the start of the first session children will be evaluated by a qualified speech pathologist with experience in the assessment of children with speech sound disorders to confirm that they fit within the inclusion criteria. This step will be accomplished by collecting a case history and include questions relating to the inclusionary and exclusionary questions as well as previous exposure to speech pathology intervention and speech pathology apps. During this assessment session, the speech pathologist will work through a checklist of instructions which are exemplary of instructions used in the therapy task to ascertain the stimulability of the therapy targets and that the child's comprehension of the instructions to be used in the experimental tasks. Errors in comprehension will be corrected by the speech pathologist within this session. Participants will be randomly assigned to a feedback condition or to the control condition and then take the pre-test. The pre-test and post-test will be offered in a room separate from the Babylab to reduce encoding specificity effects that would provide an advantage to the children in the feedback condition relative to those in the control condition. The control group will attend the first session and then return between 2 and 4 weeks later to take posttest. After completing the pretest, the experimental group will be offered 12 sessions of the experimental activities over a 4-week period. The experimental groups will then be familiarized with the Babylab. Each of sessions two to 12 will consist of approximately 10 min for the experimental task followed by approximately 10 min of an unrelated game or activity for an expected total of 20 min. Children will determine when they want to stop playing the experimental activity. As stated above, the children will complete 80–100 trials of the target minimal pairs but the exact number of trials completed by each child for each session will be recorded and checked for equity between participants. On completion of the experimental task in session thirteen, children will move from the Babylab to take the post-test. See Figure 4 for a diagram of the session schedule.

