## Proposed analysis

The assessments of speech production will be transcribed to an Excel spreadsheet. Statistical analysis will be performed using the Statistical Package for the Social Sciences (IBM SPSS Statistics 24).

The key question to be addressed in this research is: How does feedback type during speech therapy session influence children's production performance. As such, the key dependent variable under analysis will be PCC, phonological process percentage of occurrence and percentage accuracy of trials. Published data of PCC in children's development (e.g., Dodd et al., 2002) suggest that this variable to be normally distributed. As such we intend to perform a full-factorial regression analysis on PCC with feedback condition, number of trials completed, and child age (4, 5, or 6 years) and severity as predictor variables. The full-factorial nature of this analysis will allow us to determine how the effects of condition and trials completed independently predict PCC and the extent to which these factors interact in their effects on PCC between pretest and post-test. For example, we may find that with certain types of feedback, the number of trials completed has a much greater effect than with other types of feedback. Similarly, we may find that some feedback types have a greater effect on performance for younger or older children. These analyses will also be completed with phonological process percentage of occurance at pretest and post-test and percentage accuracy of trials as a dependant variables

We will also conduct a Generalized Linear Model Analysis assuming a binomial distribution for the number of correct trials post “intervention” within a total of *n* trials where *n* may differ between children. The analysis will control for pre “intervention” language skills, age, and gender. Marginal means will be compared for the five groups using a Bonferroni correction for multiple comparisons. This analysis could assist in distinguishing the effects of real-world simulation vs. verification feedback and the presence of articulation guidance.

Motivation to persevere could be considered a variable that mediates the impact of type of feedback. Consequently, we will also perform a one-way ANOVA to determine how feedback condition influences motivation as measured by the number of trials and the duration of game play.

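### A feedback arm compared with the no-game control estimates the whole game package, so it cannot show that a feedback type works in itself; the 2 × 2 comparison of types is not affected

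*Protocol article*

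**What the plan says.** Under Aims and objectives, the study is to "evaluate the efficacy within a multimedia platform of four types of feedback to assist speech development in young children"; the next sentence says that it will in particular compare types of feedback. Research question 1 asks how effective the different types are while a multimedia platform is in use.

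The Abstract describes the five conditions as "four types of feedback and a control which does not play the game". The Design section gives the purpose of the control: "A fifth condition will act as a control for changes in speech development which could occur over time, either naturally or because of other interventions". Table 4 lists context and feedback for the control as not applicable. Under Session schedule, "The control group will attend the first session and then return between 2 and 4 weeks later to take posttest", whereas "the experimental group will be offered 12 sessions of the experimental activities over a 4-week period", and "we expect that children will engage for up to 20 min completing 80–100 trials".

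In groups 1–4 the avatar speaks each word before the child does. The Design section treats this as a prompt and not as feedback: "KCR will not be provided as feedback because it will appear as a prompt when the sound is presented to the child".

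Under Proposed analysis, the generalized linear model ends with this step: "Marginal means will be compared for the five groups using a Bonferroni correction for multiple comparisons". The sentence after it says that the analysis could help to separate real-world simulation from verification feedback, and to show the effect of articulation guidance.

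**The concern.** To show that feedback is effective on a platform, the comparator has to be on the same platform without the feedback. No arm is. The control accounts for the passage of time, as the Design section says, and for nothing else that separates it from the game arms.

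The five-group comparison nevertheless treats all pairs alike. If every pair is tested there are ten, and four of them set a feedback type against control. Nothing in the article says that these four answer a different question from the other six. If practice and modelling help and the types do not differ, one or more types would often be significantly better than control. A reader with research question 1 in mind could take that as evidence that the feedback works, in a trial meant to guide what an app developer builds.

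**Working it through.** **What differs between a feedback arm and control**

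| Component | Groups 1–4 | Control | Source |
|---|---|---|---|
| Game and practice of target words | yes, 80–100 trials expected | none | Abstract; Session schedule |
| Spoken word from the avatar | yes | none | Table 4; Intervention procedure |
| BabyLab sessions | 12 offered | none | Session schedule |
| Feedback | yes | none | Table 4 |
| Assessment and pre/post-test | yes | yes | Session schedule |

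Four components change together, so the contrast identifies only their sum. Two features of the plan might seem to help, but neither does:

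- Pre- and post-tests are held in a room other than the BabyLab. This deals with familiarity with the room, not with practice, modelling or attention.
- Number of trials completed is a predictor in the regression. Controls complete no game trials, so they do not overlap with the game arms on that variable, and adjustment cannot separate practice from feedback.

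**What does not differ in this way.** Groups 1–4 have the same word set, the same basic prompt and the same session offer. Contrasts among them bear on type of feedback and on KP (articulation guidance).

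**The plan's own figure.** The protocol gives N = 150 for f = 0.32, 5% significance and 80% power, and does not name the test. For a five-group one-way ANOVA (noncentral F, λ = f²N), 80% power needs N = 122, and N = 150 gives 88.8%. The stated N is therefore not reproduced by that test. It is larger than needed, and this point does not depend on it.

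**Illustration.** Assumptions: 30 per arm, normal outcome, pooled variance on 145 df, ten pairs at 0.05/10 = 0.005 two-sided, four identical game arms, and a package effect of d SD over control. With one arm of five differing, f = d × √(0.2 × 0.8) = 0.4d, so d = 0.8 corresponds to f = 0.32. Simulated results:

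| Package effect | Each type beats control | At least one does | Some but not all four |
|---|---|---|---|
| 0.2 SD | 2% | 6% | 6% |
| 0.5 SD | 19% | 42% | 39% |
| 0.8 SD | 60% | 87% | 57% |

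In all three cases, some pair within the game arms is significant in only about 2.5% of trials.

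**Precision of the alternative contrasts at 0.5 SD**

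- One pair, 30 v 30: SE = √(1/30 + 1/30) = 0.258 and d/SE = 1.94. Power is about 18% at 0.005 and about 49% at 0.05.
- 2 × 2 main effect, 60 v 60: SE = √(1/60 + 1/60) = 0.183 and d/SE = 2.74. Power is about 78% at 0.05.
- Pooled game v control, 120 v 30: SE = √(1/120 + 1/30) = 0.204 and d/SE = 2.45. Power is about 68% at 0.05.

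Part of the gain over 18% comes from pooling arms and part from the less strict significance level.

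**The case against.** The strongest reply is that this is mainly a comparative study and says so. The second sentence of the aim is about comparing types, the design is a 2 × 2, and Outcome measurement speaks of relative benefits. The sentence after the Bonferroni step names the within-game contrasts, and every prediction of effectiveness under Anticipated results sets game arms against each other. The control is given a narrow and correct role, and the article nowhere claims that it isolates feedback. All of this stands, and it limits the point to absolute efficacy.

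Three stronger readings are tempting, and the protocol does not support them:

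- **That the trial cannot compare feedback types.** It can, through the 2 × 2 among groups 1–4.
- **That the plan will produce a false ranking of types.** That would require ranking them by which ones reach significance against control, and no such rule is stated. The five-group comparison also tests the types directly against each other. The 39% and 57% above show how such a misreading would arise; they are not the error rate of a planned inference.
- **That the game arms all receive the same fixed amount of modelled practice.** The number of trials is left to the child and is predicted to be higher with intrinsic feedback. A repeated spoken model on retries is not stated.

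The simulation also has limits. The Bonferroni step belongs to a binomial model, for which a normal outcome is a stand-in. The protocol does not give the number of pairs. Nothing in it says that the effect behind f = 0.32 lies wholly between control and the game.

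**Conclusion.** The point holds for absolute efficacy. A difference between a feedback arm and control is the effect of practice, spoken model, attention and feedback together, and a larger sample would not separate them. The first sentence of the aim and research question 1 can be read as asking for more than this contrast can give, and the analysis does not mark the control pairs as different in kind.

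The size of the risk depends on an unknown package effect. Under the stated assumptions, the chance that at least one type beats control when no type differs from another runs from about 6% at 0.2 SD to about 87% at 0.8 SD. The structural conclusion needs none of these figures; it follows from what the control arm lacks. The point is one of interpretation and choice of contrasts, worth correcting because the correction is cheap.

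**What to change.** 1. In Aims and objectives and research question 1, state two targets: the relative efficacy of the four feedback types, and the effect of the game package compared with no game.
2. In Proposed analysis, replace the comparison of all five marginal means with (a) one pooled contrast of groups 1–4 against control, labelled a package effect, and (b) the 2 × 2 contrasts among groups 1–4: intrinsic v KR, KP v no KP, and their interaction. Name (b) as the answer to research question 1, and say how multiplicity is handled over this shorter list.
3. State that types will not be judged or ranked by their significance against control.
4. State that the intrinsic v KR contrast includes the different game context shown in Table 4 and any difference in the number of trials that children choose to complete.

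Arms, sample size and visits are unchanged. The cost is that the trial no longer claims that each feedback type is effective in itself.

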### Outcome measurement

The relative benefits of the different experimental conditions will be measured by the primary measure of changes in use of phonological processes and PCC from pre-test to post-test as measured by the DEAP (Dodd et al., 2002). Such assessment will capture suppression of the phonological processes targeted in treatment and generalization effects (if any) to other phonological processes. Phonological process percentage of occurance (Randolph and Wendt, 2014; i.e., the number of times that a child uses a given phonological process) will also be measured and compared pre and posttest. Pre and post-test assessments will be recorded and a sample of the assessments independently analyzed followed by interrater reliability checks. In addition to the pre-test/post-test measures, number of trials and percentage accuracy of trials per session (cumulative accuracy) will be measured for each experimental condition as further indication of the effectiveness of feedback of that condition and determine when goals of intervention have been reached. For example, if a child reaches 90% accuracy of production of target words for one phonological process, another will be targeted. It could be argued that motivation to continue playing will increase practice and consequently improve outcomes (Williams, 2012). A secondary measure of motivation as a variable that could influence the effectiveness of feedback type will be the amount of time participants choose to continue playing the game (Deci et al., 1999) up to a total of 20 min as well as the number of trials they complete.

### Stimuli

Targets for intervention will be minimal pairs addressing the phonological processes of stopping, velar fronting and cluster reduction as, according to Dodd et al. (2002) 90% of children over 3;11 (3 years and 11 months of age) will have suppressed these phonological processes and they are therefore considered errors at this stage.

The target words comprising the minimal pairs will be:
High frequency, high imageability wordsExclude the consonants /∫/ (“sh”), /θ/ (voiceless “th”) and /ð/ (voiced “th”) as, according to Dodd et al. (2002) 90% of children by the age of 4;0 can produce all consonants except these.Exclude words with triclusters (i.e., words with three sounds in a consonant cluster such as “splash”)Initial word position as people tend to identify initial sounds more readily than medial or final sounds (Redford and Diehl, 1999).

For each phonological process addressed, five different examples for each minimal pair will be included as stimuli in the experimental tasks. For example, an experimental task targeting stopping could include the minimal pairs “fin-pin,” “see-tea,” “zoo-do,” “fat-pat,” and “zip-dip.” Hodson (2010) suggested that at least two exemplars of each phonological process be targeted in therapy. In total, 15 minimal pairs will be addressed across the experimental activities. All minimal pairs will be matched for age of acquisition, imageability and concreteness based on the MRC Psycholinguistic database and frequency using the SUBTLEX-UK database (van Heuven et al., 2014).

### Wizard of Oz setup

The “Wizard of Oz” application will be designed according to CTML principles (Mayer, 2014a,b; Clark and Mayer, 2016). The experiment will take place in the Swinburne University of Technology BabyLab which has rooms configured as per Figure 1 with microphones, speakers, cameras, desktop computers and one way windows. The speech pathologist “Wizard” will be hidden from the child. The child will play the game on a mobile tablet device and produce speech sounds as part of the game. The child's speech sounds will be transmitted to a speaker in the Wizard's room. The Wizard will see a range of feedback options on a mobile device such as a smart phone (Figure 2) and select the appropriate option which will immediately take effect on the child's tablet. Information captured by video camera and screen capture will be available for analysis.

